### Sample size

The sample size is calculated based on data on adult female *Aedes* mosquitoes collected using mechanical aspirators (15 min outdoors and indoors each) from a case-control study in nearby districts during 2016 and 2017. The mean capture was 0.78 mosquito per house (indoors + outdoors). At minimum, 34 clusters are needed to detect a 90% difference in adult female mosquitoes per house with 90% statistical power and a two-sided significance level (α) of 0.05 assuming 10 households are visited three times each after the intervention begins and a between-cluster coefficient of variation of 0.33. Sample size methods for cluster-randomized trials were used [49], as implemented in the ‘clustersampsi’ add-on to Stata® statistical software [50]. The existing data were over-dispersed relative to a Poisson distribution; therefore, to represent a negative binomial distribution with a dispersion parameter (α, or 1/*k*) of 2.03 estimated from the same data, the ‘means’ option was used, with the variance in each arm equal to the mean plus the square of the mean times α [51]. The clusters are split equally between the strata (Khon Kaen and Roi Et). To provide an equal number of clusters in each arm, one extra cluster is added per stratum, i.e., 18 clusters per stratum (city) and 9 clusters per arm in each stratum.

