#### Effect of intervention on primary outcome

For each cluster the total number of adult female *Ae. aegypti* and *Ae. albopictus* and the total number of house visits will be calculated. Taking these as summary measures, a negative binomial regression will be done with the number of mosquitoes as the outcome variable and number of house visits as the exposure (denominator) variable, i.e., with the logarithm of the number of houses as the offset. A logarithmic link function will be used. Hence, the exponential of the coefficient for arm will be the between-arm ratio in AI according to the response variable used.

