#### Effect of intervention on secondary outcomes

Dengue incidence in study households will be analyzed using negative binomial regression. The response variable will be the number of dengue cases per cluster, and the exposure will be the person-time at risk. Hence, the analysis will yield rate ratios. Multilevel models will not be used for this outcome, since the number of cases may be too small for them to be fitted robustly. The total number of DENV-infected adult female *Ae. aegypti* and *Ae. albopictus*, i.e., the IAI, will be analyzed in the same way as the AI. The number of adult mosquitoes per sticky trap will be analyzed similarly to the AI, with the exposure variable being the number of traps. This analysis will yield ratios of the ASTI. Pupae per person (number of *Ae. aegypti* pupae/person) will be analyzed similarly to the AI. The denominator of the PPI is the number of persons present per cluster summed over time. For the BI (number of containers with *Ae. aegypti* immatures/100 houses) the denominator for each cluster is the number of house collections during the intervention period. For example, if the same houses are measured at all time points, the denominator is the number of houses times the number of time points.

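### The planned negative binomial regression on 36 cluster totals tests the primary outcome at about 6–8.5% rather than 5%, and for dengue incidence it risks a zero-case arm

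*Protocol article*

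**What the plan says.** **Primary outcome.** Under Effect of intervention on primary outcome, mosquitoes and house visits are totalled for each cluster and "a negative binomial regression will be done with the number of mosquitoes as the outcome variable", with a log link and the log of house visits as offset. Statistical methods adds arm, city and the baseline value as a categorical variable; the number of categories is not given. Sample size sets 36 clusters, 9 per arm in each city, and claims "90% statistical power and a two-sided significance level (α) of 0.05". Its inputs are a mean of 0.78 per house, a house-level dispersion "of 2.03 estimated from the same data", and the following: "assuming 10 households are visited three times each after the intervention begins and a between-cluster coefficient of variation of 0.33".

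**Dengue incidence.** Under Effect of intervention on secondary outcomes, "Dengue incidence in study households will be analyzed using negative binomial regression", on cases per cluster with person-time as exposure. Multilevel models are ruled out "since the number of cases may be too small for them to be fitted robustly".

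The article names no test (Wald or likelihood-ratio), no reference distribution and no small-sample correction for either analysis.

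**The concern.** Maximum likelihood estimates the dispersion without allowing for the regression coefficients fitted alongside it. With 36 rows and four to six coefficients, the dispersion comes out too low, the standard error of the arm effect too small, and the interval too narrow. The usual large-sample tests then reject a true null more often than the 5% on which the sample size rests.

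For dengue incidence the issue is sparseness. The protocol gives small case numbers as its reason to avoid multilevel models, then chooses a model that must also estimate a dispersion and adjust for city and baseline. If one arm has no case, the rate ratio has no finite estimate. If no cluster has more than one case, nothing in the data identifies overdispersion. Without a fallback, the method for this endpoint could end up being chosen after the data are seen.

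**Working it through.** **1. The plan's own figure.** The level to be checked is two-sided 5%. The cluster count beside it ("At minimum, 34 clusters are needed to detect a 90% difference in adult female mosquitoes per house") does not reproduce. The formula is k per arm = 1 + (1.96 + 1.28)² × [(v₁ + v₂)/30 + 0.33²(m₁² + m₂²)] / (m₁ − m₂)², with v = m + 2.03m².
- 90% reduction (0.78 to 0.078): k = 3.9, so 4 per arm, 8 in total.
- 90% increase: k = 13.2, so 14 per arm, 28 in total.
- 45% reduction: k = 16.4, so 17 per arm, 34 in total.

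That is a separate point. The effect size plays no part in a calculation under the null.

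**2. Size of the excess by normal-theory analogy.** With 36 rows and p mean parameters, a maximum-likelihood standard error is too small by √((36 − p)/36). The true level is then the two-sided tail of t on 36 − p degrees of freedom beyond the shrunken critical value.

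| Baseline categories | p | Shrinkage | Level, z reference | Level, t reference |
|---|---|---|---|---|
| none | 3 | 0.957 | 7.0% | 6.0% |
| 2 | 4 | 0.943 | 7.4% | 6.4% |
| 3 | 5 | 0.928 | 7.9% | 6.8% |
| 4 | 6 | 0.913 | 8.4% | 7.2% |

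Example for 3 categories: 1.96 × 0.928 = 1.819, and P(|t₃₁| > 1.819) = 7.9%.

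**3. Simulation of the planned model under no effect.** Inputs: 36 clusters, 9 v 9 within each city, 30 visits, mean 0.78, house dispersion 2.03, gamma cluster means with coefficient of variation 0.33, baseline sharing the cluster effect. There were 2,400 to 5,000 runs per setting (Monte Carlo standard error about 0.4 to 0.6 points).

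- Wald z: 6.7–7.6% without baseline; 8.0%, 7.6% and 7.9% with 2, 3 and 4 categories.
- Likelihood-ratio: 5.8–7.3%.
- Wald with t reference: 5.6–6.9%.
- Linear model of cluster log rates, t reference: 4.0–5.3%.

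A further 4,000 runs per setting gave 8.1–8.2%, 7.3–7.5%, 7.0–7.3% and 4.3–5.4% in the same order. Wald z stays at 8.3–8.7% with a coefficient of variation of 0.2 or 0.5, a mean of 0.4, or 57 visits (30 plus 3 sentinel houses × 9 other months). The worst likelihood-ratio and t results listed are at mean 0.4: 8.0% and 7.6%.

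**4. Expected dengue cases.** Each city has 18 × 10 = 180 houses, followed for about one year after the intervention starts. Household size is not stated; 3 to 5 persons (h) is assumed. Two sets of rates can be taken from Setting.
- Stated district incidences: 180 × h × (455.3 + 329.1)/100,000 = 4.2, 5.6 and 7.1 cases for h = 3, 4 and 5.
- Stated mean cases over stated populations: 655/400,000 = 164 and 360/160,000 = 225 per 100,000, giving 2.1, 2.8 and 3.5 cases.

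**5. Chance of a zero-case arm, no effect.** For Poisson counts with E expected cases in total, P = 2e^(−E/2) − e^(−E).
- E = 4.24: 2 × 0.120 − 0.014 = 0.23; E = 7.06: 0.06.
- E = 2.10: 2 × 0.350 − 0.122 = 0.58; E = 3.50: 0.32.

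Letting cluster rates vary (dispersion up to 1), simulation gives 6–25% at the stated incidences and 31–59% at the derived rates. With a true rate ratio of 0.5 these become 20–45% and 52–74%.

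**6. Dispersion.** The chance that no cluster has more than one case, under no effect, is 37–79% at the stated incidences and 75–94% at the derived rates. The fit then falls back to Poisson. With 5 expected cases (between-cluster coefficient of variation 1.0), a default negative binomial fit failed in 62% of 500 runs, yet a finite arm estimate existed in 80%. With 10 cases the figures were 34% and 97%.

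**The case against.** The article fixes the model but not the test. A statistical analysis plan that is not shown may specify a reference distribution or a correction, and the 8% figure belongs only to the default Wald z test. That stands, and a reader should not infer that the plan as written tests at 8%. It does not remove the point. The choice of this regression on 36 totals is made here, and the likelihood-ratio test and t reference also average above 5%, while a simple cluster-level alternative does not.

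For dengue incidence, a reader might infer that the rate ratio will usually be inestimable. The documents do not support that. At the stated incidences a zero-case arm occurs in a minority of null trials, and a fit that collapses to Poisson still yields a ratio. The case numbers also rest on an assumed household size and on routine reporting, whereas the trial uses weekly active fever detection. At three times the Khon Kaen rate (15–25 cases), a zero-case arm has a chance below 0.5%. Against that, a case needs both a positive rapid test and a positive RT-PCR, and Study limitations itself anticipates too few infections. The protocol is also open that incidence is secondary because an adequate sample is not feasible.

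It is tempting to extend the point to infected mosquitoes (the infected adult index), which are analysed the same way. The documents give no mosquito infection rate, so nothing can be said about its size.

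**Conclusion.** The concern holds in this limited form. For the primary outcome the stated model is anti-conservative by roughly 1 to 3.5 percentage points: about 7–8.5% with Wald z and about 6–7.5% with a likelihood-ratio test or t reference. This rests on the protocol's own mean, dispersion, coefficient of variation and visit count, and changes little when they are varied. The excess is modest, but it affects the main p value and interval of the trial.

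For dengue incidence the risk of a zero-case arm is substantial, at 6–25% or 30–60% under no effect depending on which of the document's rates is used, and higher if the intervention works. The dispersion is often not identifiable. Both statements assume 3–5 persons per house and no extra yield from active detection. The change should be made; it does not call the design into question.

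**What to change.** **Primary outcome.** Keep the negative binomial rate ratio as the point estimate. Take the p value from a permutation test that re-randomises arm within city, 9 v 9. This mirrors the lottery under Sequence generation and implementation, and there are 48,620 possible allocations per city. Obtain the interval by inverting that test. Alternatively, use a linear model of cluster log rates with arm, city and baseline and a t reference, for both p value and interval. The second option needs a stated rule for clusters with no mosquitoes: under the assumed 90% reduction an intervention cluster expects only 30 × 0.78 × 0.1 = 2.3.

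**Dengue incidence.** Use the same within-city permutation test on cluster case totals over person-time. Report the ratio descriptively, and state in advance what is reported if an arm has no case. Do not attach exact Poisson or binomial intervals, which ignore variation between clusters.

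**Cost.** A little more programming and slightly wider intervals. No change to data collection or sample.

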#### Effect of intervention on secondary outcomes

Dengue incidence in study households will be analyzed using negative binomial regression. The response variable will be the number of dengue cases per cluster, and the exposure will be the person-time at risk. Hence, the analysis will yield rate ratios. Multilevel models will not be used for this outcome, since the number of cases may be too small for them to be fitted robustly. The total number of DENV-infected adult female *Ae. aegypti* and *Ae. albopictus*, i.e., the IAI, will be analyzed in the same way as the AI. The number of adult mosquitoes per sticky trap will be analyzed similarly to the AI, with the exposure variable being the number of traps. This analysis will yield ratios of the ASTI. Pupae per person (number of *Ae. aegypti* pupae/person) will be analyzed similarly to the AI. The denominator of the PPI is the number of persons present per cluster summed over time. For the BI (number of containers with *Ae. aegypti* immatures/100 houses) the denominator for each cluster is the number of house collections during the intervention period. For example, if the same houses are measured at all time points, the denominator is the number of houses times the number of time points.

#### Prediction

The study will attempt to predict dengue incidence over time using entomological and immunological indices based on repeated (monthly) field collections. This will be done in two ways: by predicting the risk of a future outbreak, and by estimating associations between dengue incidence and the indices.

##### Predict the risk of a future outbreak within a week or within a longer lead time

According to the Ministry of Public Health, an outbreak is defined as the number of cases per week exceeding the median number of cases during the last 3–5 years. We will have data on the stated indices 1 week every month, as opposed to every week, so approximately one quarter of the dengue case series data will be able to be used in this analysis.

Using logistic regression, we will develop a prediction rule for the outbreak status (i.e., outbreak or not) in a given week based on data on the indices and on climate, in the previous week or earlier. Climate variables will include rainfall amount and frequency and ambient maximum and minimum temperatures. We will also consider other variables related to housing type and socioeconomic status at the spatial level to be predicted. The aim of the analysis will be to obtain a rule with a high negative predictive value, i.e., with most of the negative predictions being borne out, and with few outbreaks being missed. We will also calculate other operating characteristics such as sensitivity and specificity. We will concentrate on trying to predict outbreaks from one week to the next, i.e., with a lag of 1 week, but will also assess rules for lags up to 4 weeks.

The accuracy of this prediction rule will be assessed by developing it on the majority of the data as a “training” dataset, then evaluating it on the remainder of the data as a “test” dataset. This reduces the tendency to over-estimate the accuracy of prediction when the evaluation is done on the same dataset from which the rule was developed.

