The WHO Global Strategic Framework for integrated vector management (IVM) was released in 2004 and recommends a range of interventions, in combination, to increase impact [41]. This means there is no single vector control method that is effective enough to control both vector populations and disease transmission. Combinations of larval control interventions, such as mixtures of pyriproxyfen (an insect growth regulator) and spinosad (a biopesticide) have been evaluated. This combination reduced larval and pupal relative densities by 90% for at least 4 months in the French West Indies [42]. Pyriproxyfen, even in minute doses, can induce complete inhibition of adult emergence for several weeks after treatment [43]. Pyriproxyfen used alone and applied to storm drains in Colombia reduced dengue cases by 80% [44]. The benefit of using these two compounds in combination is that they have different modes of action and that pyriproxyfen targets the pupal stage while spinosad is active against larval stages. Both compounds have very low toxicity for humans and most other non-target fauna [45, 46]. The WHO draft on global vector control response for 2017–2030 [47] builds on the IVM approach but places stronger emphasis on enhancing human capacity and health education, increasing research and innovation by strengthening infrastructure, and increasing intersectoral and interdisciplinary action. The targets of the global response are to reduce mortality and incidence due to all vector-borne diseases globally relative to 2016 by at least 75% and 60%, respectively.

In view of the preceding discussion, this study aims to assess a specific vector control intervention and to contribute to the development of a practical early warning system that can more accurately predict changes in dengue transmission and impending outbreaks. The trial will determine the efficacy of a pyriproxyfen/spinosad combination in water storage containers to reduce entomological risk indicators and dengue incidence. The hypothesis is that the study arm receiving the combination treatment in household water storage containers will have a lower density of adult female *Ae. aegypti* per house, both indoors and outdoors, compared to the study arm receiving an alternative intervention involving normal governmental action. Furthermore, the study aims to determine one or more entomological indices and an immunological index that best predicts dengue incidence for the study area.

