This trial is also designed to identify practical and sensitive entomological and immunological indicators for prediction of dengue transmission and increased risk for dengue outbreaks. The more accurate, timely, and site-specific the prediction, the greater the likelihood a control response would mitigate, if not prevent, the outbreak from occurring. The originality of this trial is that virological and immunological methods are used in combination with standard entomological measures in both intervention and control clusters. The Peru study mentioned previously [17] investigated the relationship between indicators of mosquito abundance and DENV infection. Although, it is probably one of the most comprehensive studies to date, such abundance-based indicators are not likely to be sensitive enough to detect changes in intensity of transmission. A better indicator would be to monitor adult mosquitoes for dengue viral infection, similarly as is done to assess malaria transmission risk using the entomological inoculation rate. RDTs can be used as a simple method to detect DENV antigen in mosquitoes [77, 78]. New methods to monitor DENV-infected adult *Aedes* densities using various trapping designs and RDTs have been proposed as a new paradigm in *Aedes* surveillance [79, 80].

Another potentially promising indicator is to measure the exposure of people to mosquito bites using human antibody response to mosquito salivary protein. A recent study carried out along the Thai-Myanmar border areas demonstrated that levels of IgG response were positively associated with anopheline vector abundance and the entomological inoculation rate [81]. The antibody response to *Ae. aegypti* whole saliva has been shown to be a quantitative biomarker of human exposure in Africa and South America [82, 83]. More recently, a salivary peptide (Nterm-34 kDa) was identified as a specific *Aedes* biomarker [84, 85]. The IgG immune response to Nterm-34 kDa salivary peptide is not expected to last for more than 15–30 days; hence, it represents a relevant temporal biomarker to assess recent relative exposure of humans to *Aedes* bites [84]. This peptide was used successfully as a short-time indicator to evaluate vector control interventions against *Aedes* exposure in Réunion Island [86].

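### The outbreak rule is scored on weekly outbreak status pooled over all usable weeks, so its accuracy does not by itself show that it warns of impending outbreaks

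*Protocol article*

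**What the plan says.** The section on predicting the risk of a future outbreak fixes four things.

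- **Response.** Logistic regression is used: "we will develop a prediction rule for the outbreak status (i.e., outbreak or not) in a given week based on data on the indices", together with climate and possibly housing and socioeconomic variables, all from the previous week or earlier.
- **Definition.** The Ministry's rule is adopted, under which "an outbreak is defined as the number of cases per week exceeding the median number of cases during the last 3–5 years". This labels single weeks. It has no criterion for onset, duration or end.
- **Weeks used.** "We will have data on the stated indices 1 week every month, as opposed to every week". By the article's own reckoning, roughly 25% of the weekly series is then available. Index availability is the only stated limit on which weeks enter.
- **Scoring.** "The aim of the analysis will be to obtain a rule with a high negative predictive value", with few outbreaks missed. Sensitivity and specificity are also calculated, and a test set is held out. The main rule works "with a lag of 1 week, but will also assess rules for lags up to 4 weeks".

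The purpose is given elsewhere. The Background wants to contribute to "a practical early warning system that can more accurately predict changes in dengue transmission and impending outbreaks". The Discussion opens with the same aim and later argues that the more accurate and timely the prediction, "the greater the likelihood a control response would mitigate, if not prevent, the outbreak from occurring".

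**The concern.** A warning is useful when the outbreak has not yet begun. The planned scoring gives the same credit for calling a week that continues an outbreak as for calling the first week of one. Weekly dengue counts are usually serially correlated, so outbreak weeks tend to follow outbreak weeks. An index that rises and falls with current transmission, with no lead over it, can then earn much of its sensitivity and NPV from continuation.

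The lags do not remove this. They ensure that the predictors precede the week being scored, but not that the outbreak was still to come when they were measured.

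At stake is the interpretation of the prediction part of the trial. A rule could be reported as a sensitive early warning on figures that mostly reflect recognition of outbreaks already under way. The comparison of arms on the Adult index is not affected.

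**Working it through.** **1. The plan's own figure.** Twelve index weeks a year out of 52.18 is 12/52.18 = 0.23, which agrees with the stated one quarter. Over 24 months this is about 24 index weeks per city, or 48 city-weeks. The protocol does not fix the spatial level of prediction, so city level is an assumption.

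**2. What pooled sensitivity contains.** Let c be the share of outbreak weeks that follow a week already in outbreak. Then

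pooled sensitivity = c × (sensitivity in continuing weeks) + (1 − c) × (sensitivity at onset).

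The pooled figure alone does not determine the onset term. At 80% pooled sensitivity, if every continuing week is called correctly, onset sensitivity is (0.80 − c)/(1 − c). This is 0.43 at c = 0.65 and 0.20 at c = 0.75.

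**3. A benchmark with no warning ability.** Take a two-state chain with outbreak share π and mean run L weeks (both assumed), and a rule that only repeats last week's status. Its sensitivity is P(outbreak to outbreak) = 1 − 1/L. Its NPV is P(no outbreak to no outbreak) = 1 − (1/L) × π/(1 − π).

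| L (weeks) | Sensitivity, lag 1 | NPV, π = 0.5 | NPV, π = 0.3 |
|---|---|---|---|
| 4 | 75% | 75% | 89% |
| 8 | 87.5% | 87.5% | 95% |
| 12 | 91.7% | 91.7% | 96% |
| 20 | 95% | 95% | 98% |

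By construction it detects no onset. At lag 4 with π = 0.5 its sensitivity and NPV are still 53% to 83%.

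**4. An index that tracks current transmission.** The inputs were weekly Poisson counts with the district means in the Setting section (655 and 360 cases a year) and a seasonal cycle. Lag-1 autocorrelation on the log scale was 0.90 to 0.97, with SD 0.6 to 0.7. An outbreak was a count above the same-week median of the previous five years. The index had correlation 0.5 to 0.8 with current transmission. Only the means come from the document. Across repeated runs:

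- continuing weeks were 65% to 84% of outbreak weeks;
- at 80% pooled sensitivity, continuing weeks were caught 82% to 88% of the time and onsets roughly 60% to 71%.

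These agree with step 2. With c = 0.75 and onset sensitivity 0.61, the continuing-week value is (0.80 − 0.25 × 0.61)/0.75 = 0.86.

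**5. NPV needs its base rate.** In the same setting, 72% to 78% of weeks that start out of outbreak stay out. Always predicting no outbreak would score that NPV among them.

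**6. How many onsets are usable.** The complete weekly series holds about 26 to 31 onsets over both cities in two years. With indices in 12 of 52 weeks, 26 × 12/52 = 6.0 and 31 × 12/52 = 7.2. Allowing for stronger persistence, about 4 to 7 is a fair range. The chain in step 3 gives 0.7 to 6.0 at lag 1. For scale, 4 of 6 onsets detected has an exact 95% interval of 22% to 96%.

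**The case against.** Four arguments on the other side deserve weight.

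**The response matches the stated objective.** The Objectives section speaks of predicting variation in dengue incidence over time, and the Outcomes section of outbreaks as the Ministry defines them, which is a weekly status. A second planned analysis relates lagged indices to weekly case counts. This stands. A reader might infer that the second objective is answered for the wrong event, but the documents do not support that. The gap is between the scoring and the early-warning aim in the Background and Discussion.

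**Onsets are too few.** This also stands, and it limits the remedy. A reader might infer that the rule should be developed and chosen only on weeks not yet in outbreak, relying on 26 to 31 onsets. That count ignores the one-quarter limit. With about 4 to 7 usable onsets, split between training and test data, a rule with several indices and climate terms could not be usefully selected.

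**The size is assumed.** Autocorrelation, spread and index correlation are not in the document, and the simulated index was specified to follow current transmission. The repeat-last-week rule is a benchmark and not the planned model, since current outbreak status is not a listed predictor. A reader might infer that the planned rule would miss all onsets or fail. Neither calculation shows that. With runs averaging 3 to 4 weeks and one scored week a month, a single outbreak also seldom earns repeated credit. The share of scored outbreak weeks that are continuations is nevertheless unchanged by sampling one week in four.

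**It is a reporting detail that an analysis plan could add.** It could, and nothing in the protocol forbids it. But the protocol itself fixes the response, the target and the accuracy measures, and as written they do not address warning.

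**Conclusion.** The concern holds in a limited form. Accuracy over all usable weeks mixes recognition of continuing outbreaks with warning of new ones, so high NPV and sensitivity do not by themselves show that the rule warns of impending outbreaks. Under the assumed autocorrelation, 80% pooled sensitivity corresponds to roughly 60% to 71% at onset, so 29% to 40% of onsets are missed where the pooled figure suggests 20%. The size depends on persistence, on the threshold and on how closely the index follows current transmission. The logical point does not. It is a moderate overstatement of warning ability that is cheap to expose. It does not mean that the planned rule has no value.

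**What to change.** Keep the logistic rule fitted on all usable weeks, with the planned pooled accuracy figures. Add the following to the analysis text:

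- Classify each scored week t by outbreak status at week t minus the lag, and define an onset accordingly.
- For weeks not in outbreak at that point, report sensitivity and NPV separately at each lag from 1 to 4 weeks, with the number of onsets, the base rate of no outbreak and confidence intervals.
- Treat these results as descriptive, and do not refit or select the rule on these weeks alone.
- Limit any early-warning claim to this result.

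The cost is a few lines of text and code, using case data already held. The drawback is imprecision: with about 4 to 7 usable onsets at lag 1 over both cities, the intervals will be wide and may support no firm conclusion about warning ability.
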